## Abstract

**Background:**

Dental prostheses, which aim to replace missing teeth and to restore patients’ appearance and oral functions, should be biomimetic and thus adopt the occlusal morphology and three-dimensional (3D) position of healthy natural teeth. Since the teeth of an individual subject are controlled by the same set of genes (genotype) and are exposed to mostly identical oral environment (phenotype), the occlusal morphology and 3D position of teeth of an individual patient are inter-related. It is hypothesized that artificial intelligence (AI) can automate the design of single-tooth dental prostheses after learning the features of the remaining dentition.

**Materials and methods:**

This article describes the protocol of a prospective experimental study, which aims to train and to validate the AI system for design of single molar dental prostheses. Maxillary and mandibular dentate teeth models will be collected and digitized from at least 250 volunteers. The (**original**) digitized maxillary teeth models will be duplicated and **processed** by removal of right maxillary first molars (FDI tooth 16). Teeth models will be randomly divided into **training** and **validation** sets. At least *200* training sets of the original and the processed digitalized teeth models will be input into 3D Generative Adversarial Network (GAN) for training. Among the validation sets, tooth 16 will be **generated by AI** on *50* processed models and the morphology and 3D position of AI-generated tooth will be compared to that of the natural tooth in the original maxillary teeth model. The use of different GAN algorithms and the need of antagonist mandibular teeth model will be investigated. Results will be reported following the CONSORT-AI.

## Introduction

### Background

#### Missing teeth and its consequences

Missing teeth, either congenital or consequent to dental diseases or trauma, is commonly seen and deteriorates patients’ health, well-being, and quality-of-life [1, 2]. Epidemiological studies have projected a trend of increasing missing teeth and deterioration of oral health due to the aging [3, 4] of the society, and efforts are needed to prepare for the spike of needs in health resources.

#### Biomimetic dental prostheses

By replacing the missing teeth, dental prostheses aim to restore appearance and oral functions of a patient, thus restore patient’s quality of life. The prevalence of single tooth loss is the most observed pattern of tooth loss. For the best prosthodontic prognosis and restoration of functions, dental prostheses should be biomimetic [5, 6] and thus adopt the occlusal morphology and 3D position of healthy natural teeth. These features sustain the functional equilibrium of dentition such as the bucco-lingual position as well as the occlusal relationships, and any disturbance to this equilibrium may result in pathology of the teeth and thus oral dysfunctions. It has always been a challenge to reconstruct original morphology on the dental prostheses, and treatment outcome tend to vary, subjecting to errors and failure [7]. Thus, a more personalized approach in designing prostheses is needed [8, 9].

#### Limitation of Computer-Assisted Design (CAD)

Despite the wide application of CAD software, the use of virtual patient models and virtual articulators [10–12], as well as the preformed tooth morphology libraries facilitates designing dental prostheses over a shorter period, considerable time is still required to fit the dental prostheses into patients’ occlusion clinically [13, 14]. The tooth morphology generated by these libraries do not fits in the individual patients. The duplication of the original tooth or “flipped” of the contralateral tooth, if present, requires the correct 3D tooth position, otherwise occlusal interferences will still result and requires significant clinical adjustments. Moreover, the inputs of dentists and dental technicians are still necessary, and the design process can still be lengthy, regardless of the approach taken for impression/scanning and fabrication process [15].

#### Artificial Intelligence (AI) as solution

The use of AI and dental robots are considered as the trend of automated digital dentistry that may reduce the manpower costs, and AI models have shown the potential of being a reliable tool on various dental treatment process [16, 17]. AI is defined as “the capability of a device to perform functions that are normally associated with human intelligence such as reasoning, learning, and self-improvement” [18]. With adequate trainings, AI may perform tasks that in the past require human intelligence, and in connection with this, AI may help designing dental prostheses. Since the teeth of an individual subject are controlled by the same genes (genotype) [19], and all teeth are exposed to mostly identical oral environment (phenotype), the occlusal morphologies and 3D positions of a subject’s teeth are inter-related. By taking reference to the natural dentition, the prostheses in questions should be able to retain the original functionality and to have no interference to the jaw movements. It is hypothesized that using a 3D Generative Adversarial Network (GAN) [20, 21], AI can learn the morphology and positional relationship between teeth in an individual subject and automate the design of biomimetic single-tooth dental prostheses from the features of the remaining dentition after sufficient trainings.

#### Generative adversarial networks

The AI trainings in dentistry are mostly on the 2D radiography and 3D tomography [22, 23]. To the best knowledge of the authors, there is no clinical study on the AI learning of 3D teeth models. Four GAN approaches, namely voxel-based, view-based, point-based, and fusion methods, are currently used to train the 3D models [24] and this study investigates if there are any differences in these approaches in the AI training for 3D teeth models.

#### Antagonist teeth models

Regarding the prediction of occlusal morphology, studies have shown that the presence of antagonist teeth models helps in setting the limit of occlusal morphology [25]. It is unknown if the same is applied to the AI learning and predicting of the occlusal morphology.

### Objectives

To compare the occlusal morphology and 3D position of the AI-generated single-tooth dental prostheses with reference to healthy natural tooth.
To determine the appropriate AI deep-learning methods/algorithms that should be used in interpreting and learning of the features of 3D teeth models.To determine if the antagonist (mandibular) teeth models should be used in the AI training.

## Study protocol

### Materials and methods

#### Collection of teeth models

This study is designed in accordance with the Standard Protocol Items: Recommendations for Interventional Trials (SPIRIT) guidelines [26] (Fig 1).

**Fig 1 pone.0268535.g001:**
[figure not shown]
SPIRIT diagram showing the schedule of enrollment, allocation, interventions, and assessments of this study. –t_1_  =  baseline assessment (before randomization), 0 (t_0_) = randomization, t_1_ = after randomization, t_2_  =  25% of collected models learnt by AI, t_3_  =  50% of collected models learnt by AI, t_4_ = 75% of collected models learnt by AI, t_5_  =  100% of collected models learnt by AI, t_6_ = the whole study is completed.

Maxillary and mandibular dentate teeth models will be collected from at least 250 volunteers [27], consisting of patients attending the University teaching hospital (Prince Phillip Dental Hospital) as well as the students of the University of Hong Kong. Participants will be screened and selected according to the following inclusion and exclusion criteria:

#### Inclusion criteria

**Subject level**:

Subjects with more than 12 functional occlusal units and stable maximal intercuspal position (MIP) [28].Subjects who have the right maxillary first molar tooth.Subjects who did not undergo orthodontic treatment and/or did not have teeth that rotated more than 45 degrees and/or displaced more than 1.5 mm [29].

**Tooth level**:

Sound tooth or tooth with single surface restorations that do not grossly alter its morphology.

#### Exclusion criteria

**Subject level**:

Subjects with periodontal disease (Basic Periodontal Examination BPE Score 3) whereby there may be pathological tooth migration and alteration of occlusal plane.Subjects who are under the age of 18 and unable to give consent.

**Tooth level**:

Teeth with extensive (two or more surfaces) restorations that affect the morphology.Teeth that have pathological tooth movements such as fremitus, drifting, and overeruption.

Subjects will be first screened for eligibility at the subject-level. Individual teeth in these recruited subjects will then be assessed for eligibility at tooth-level.

### Preparation of teeth models

Teeth models will be collected and digitized using laboratory scanner (Trios D2000; 3Shape, Denmark) into Standard Tessellation Language (STL) format by one operator and the quality will be checked by another operator.

Digitized models in STL format will be converted into Polygon File Format (PYL) using MeshLab (v2021.07, Visual Computing Lab of the ISTI-CNR) [30]. The converted files will be duplicated into two identical sets, with one set of files with **original** maxillary arch and one set of files with the right maxillary first molar (FDI World Dental Federation Notation 16) removed from the arch using MeshLab to simulate a missing tooth i.e. **processed** (Fig 2).

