**Fig 2 pone.0268535.g002:**
[figure not shown]
General flow of processing collected data.

Collected teeth models will be randomly divided into **training** and **validation** sets.

At least two-hundred **training** sets including the **original** and the **processed** models will be input into the AI system to learn the relationship between individual teeth (tooth 16) and rest of the dentition via a 3D Generative Adversarial Network (GAN) designed for this study (Fig 3). Data will be computed by the High-Performance Computer provided by the Information Technology Services (ITS), The University of Hong Kong (HKU), which is capable of conducting data intensive and accelerated computing using a high-performance computing cluster with an aggregating processing power of 804 TFlop/s (Fig 4).

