**Fig 3 pone.0268535.g003:**
[figure not shown]
Brief architecture of the Generative Adversarial Network (GAN) of this study. Original model: digitized maxillary teeth model collected from participants; processed model: teeth model with tooth 16 removed; Generated model: teeth model with AI-generated tooth 16.

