#### Validation of AI system

Separate (50) sets of the original and the processed maxillary teeth models will be serve as validation sets. The effectiveness of the four deep learning algorithms in predicting the occlusal morphology and 3D position of single missing tooth (tooth 16) on the processed models will be evaluated and compared to the natural tooth 16 on the original models.

After determining the appropriate GAN algorithm, the need of antagonist mandibular teeth models in AI predicting the occlusal morphology and 3D position of single missing maxillary tooth will be evaluated.

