### Outcome measurement

The progress of the AI training will be evaluated with quartiles analysis. The following indicators of AI-designed prostheses will be examined at least 4 times during the training procedure, when 25%, 50%, 75% and 100% of collected teeth models have been learned respectively by the AI system. The morphology, i.e., geometric morphometric, and 3D positions, of tooth 16 designed by the trained AI system will be assessed by comparing to the corresponding natural teeth among the validation sets.

**a) Occlusal morphology. 1. Matching of trimmed tooth 16 to its respective arch–**The processed models and their trimmed original tooth 16 of the validation sets will be anonymized. The AI generated tooth 16 on these processed models will be used as a guide to match the trimmed original tooth 16 to its corresponding arch. The individual trimmed original tooth 16 will be best fit superimposed to the AI generated tooth 16 on these processed models. Hausdorff distance (HD) showing the degree of match will be obtained and the trimmed original tooth with the least HD will be regarded as best fitting and will be matched to this processed model [36]. The percentage of correct matching will be reported.

**2. The geometric morphometric of AI generated tooth**–the cusp tips (highest point), fossae (lowest point) and cuspal inclines (joining the cusp and fossa) of the individual cusps will be compared to the original tooth 16 by best-fit superimposition and their differences will be analyzed (Fig 7A).

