**Fig 7 pone.0268535.g007:**
[figure not shown]
A & B: Superimposition of teeth for comparison (left). Measurement of the geometric morphology and 3D position by locating the anatomical landmarks of a tooth such as cusp tips and fossae as well as the center of a tooth (arrowed) respectively (right).

**3. Functional occlusal morphology**–the maxillary and mandibular teeth models will be mounted to a virtual articulator (exocad; DentalCAD, exocad) at average setting and the whole system is instructed to perform simulated jaw movements to determine if there is any occlusal interference [9, 37].

**b) 3D position.** The center (and its coordinate) of the AI generated tooth and the original tooth 16 will be determined by the software (Fig 7B). Using the adjacent teeth as reference area for best-fit superimposition, the buccal and lingual contours of the AI generated tooth and the original tooth will be compared, and their differences will be observed both visually as well as in HD.

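### As described, deleting tooth 16 from a dentate scan can leave its outline in the AI input, so position, contour and (through size and outline only) matching results are open to inflation of unknown size

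*Protocol article*

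**What the plan says.** Preparation of teeth models says of the scan files: "The converted files will be duplicated into two identical sets". One set keeps the full upper arch. The other is "one set of files with the right maxillary first molar (FDI World Dental Federation Notation 16) removed from the arch using MeshLab to simulate a" tooth gap. The legend to Fig 3 adds nothing further: "processed model: teeth model with tooth 16 removed".

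At least 200 original/processed pairs train the network "to learn the relationship between individual teeth (tooth 16) and rest of the dentition". Fifty further pairs serve for validation, where the algorithms are judged on "predicting the occlusal morphology and 3D position of single missing tooth (tooth 16) on the processed models".

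Two groups of results under Outcome measurement matter most here. For matching, "The AI generated tooth 16 on these processed models will be used as a guide to match the trimmed original tooth 16 to its corresponding" dental arch, and the natural tooth with the smallest Hausdorff distance is taken as the match. For 3D position, "The center (and its coordinate) of the AI generated tooth and the original tooth 16 will be determined by the software", and the buccal and lingual contours of the two teeth are compared.

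**The concern.** The Introduction's hypothesis is that a network can infer a missing tooth from the teeth that remain. To test this, the input must carry no trace of the tooth to be predicted. A processed model made by deleting one tooth from a scan taken with that tooth in place may still carry one: the edge of the cut, the gingival margin around the tooth, and the boundary with teeth 15 and 17.

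If that trace stays in, a network could centre a crown on the gap and size it to the outline while learning little from the other teeth. Good position, contour and matching results could then not be attributed to the hypothesis. Holding out 50 subjects would not reveal this, because their models are prepared in the same way.

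**Working it through.** **1. Tracing the input.** The article describes a copy of the dentate scan with tooth 16 deleted. It describes no gap closure, standard cut or masking of the margin. Training and validation use the same kind of processed model. Eligibility requires tooth 16 to be present, so no validation case is a true gap. The further validity work named in the Discussion covers orthodontic and periodontal subjects only. Nothing planned would therefore separate an outline cue from inference.

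**2. Which outcomes an outline could inform.**

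| Outcome | How it is compared | Exposure to an outline cue |
|---|---|---|
| Tooth centre | Coordinates of generated and natural tooth | Direct |
| Buccal and lingual contours | Superimposed on the adjacent teeth | Direct; location and width both count |
| Correct matching | Natural tooth best-fitted onto generated tooth, then least Hausdorff distance | Size and outline only; best fit removes location |
| Cusp tips, fossae, cuspal inclines | Best fit of the two teeth | Little; these lie on the deleted crown |
| Occlusal interference | Virtual articulator | Little, for the same reason |

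**3. Figures in the plan.** 200 training + 50 validation = 250 volunteers, as stated. Matching by chance among 50 teeth is 1/50 = 2%. The documents give no figure from which a leak could be sized.

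**4. Two illustrations. All inputs are assumed.** Each uses 50 teeth, 400 runs and nearest-distance matching.

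*A. Only leaked dimensions enter the match.* There are k independent outline dimensions with between-subject SD 0.5 mm, read with error SD 0.1 / 0.2 / 0.3 mm. Correct matches:
- k = 2: 55.5 / 29.8 / 19.3%
- k = 4: 95.4 / 70.6 / 46.8%
- k = 6: 99.8 / 91.2 / 71.7%

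*B. Eight standardised features, of which two or four are leaked.* Leaked features are read with error 0.6 to 0.3 SD. The others are predicted from the remaining teeth with correlation r. Correct matches:

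| r | No leak | 2 leaked | 4 leaked |
|---|---|---|---|
| 0 | 2.0% | 10.3–12.5% | 29.4–38.4% |
| 0.3 | 3.4% | 13.9–16.7% | 33.5–43.3% |
| 0.5 | 9.3–9.4% | 23.6–28.0% | 43.5–55.8% |
| 0.7 | 33.2–33.3% | 47.9–54.5% | 62.5–76.0% |

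B is the more cautious model because unleaked features also enter the distance. Without a leak, the error of a feature is √(1 − r²); at r = 0.5 this is √0.75 = 0.87 SD (simulated 0.86). With a leak it is simply the assumed 0.30–0.60 SD, so that part is not evidence of size.

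Both models show direction: matching well above 2% can occur when the other teeth carry no information (r = 0). Neither uses the plan's full-surface Hausdorff distance, and neither estimates what this study would find.

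**5. A check that does not work.** One might place a mean tooth in every gap and see whether matching exceeds 2%. One fixed shape, best-fitted to the same 50 natural teeth, selects the same tooth each time. It is right for exactly one arch, 1/50 = 2%, leak or no leak.

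**The case against.** The strongest reply is that the decisive fact is not on the page. The article does not say where the cut runs or that the gap is left open, and Fig 2, which illustrates the processing, is not shown. A condensed article may leave mesh editing to the full protocol. It also does not say that the trimmed tooth and the gap share one cut edge. Further, matching uses best-fit superimposition, and crown mismatch still counts in a whole-surface distance. Neighbouring teeth and arch form legitimately indicate position, so good positional accuracy is not by itself leakage. The simulation inputs have no source in the documents.

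All of this stands and limits the claim. A reader might infer that the hole certainly has the tooth's shape and that accuracy is inflated; the text supports only that it can be. A reader might also infer that the antagonist comparison is biased towards finding the lower model unnecessary. The article gives the antagonist's role as providing occlusal contacts and limiting cusp height, which an outline does not supply, so that bias is not shown. Nor do the documents contain anything showing that performance would fall at a real edentulous site.

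The reply does not remove the point. How the network's input is made is part of the design, and the article does describe it. Followed as described, the preparation has no step that removes the trace, and validation could not detect it.

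**Conclusion.** The point holds in conditional form. As described, the natural tooth's outline can remain in the AI input in both sets. Tooth centre and buccal and lingual contours are directly open to inflation, and correct matching is open to it through size and outline. These results may therefore not reflect inference from the remaining teeth. Cusp, fossa, incline and interference results are much less exposed.

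The size is unknown. Under the cautious illustration with uninformative neighbours, matching goes from 2% to about 10–13% (two leaked features) or 29–38% (four). Those figures rest wholly on the assumed number of features, their independence and the reading error.

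The conclusion assumes that no masking step exists in a fuller document. If one does, a sentence saying so settles the matter. If not, it should be settled before training, because the later remedy is to reprocess the models and retrain.

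**What to change.** State the cut line and the gap treatment. Before training, delete a standard region between teeth 15 and 17, defined from those neighbours and extending beyond the gingival margin of 16. Close it with a surface built from the neighbours only. Apply this identically to training and validation models.

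At minimum, repeat the position, contour and matching analyses with the margin masked, as a sensitivity analysis. This should include retraining on masked models, since a network trained on unmasked input could do worse merely because masked input is unfamiliar.

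As a benchmark, report the position error of a mean tooth placed from the neighbours only against that of one placed at the centroid of the cut edge. If the second is clearly smaller, the gap carries positional information beyond what the neighbours give. Do not use mean-tooth matching as a check, for the reason in step 5 of the working.

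The cost is one scripted mesh step per model and a wording change, with no new subjects or scans. The sensitivity analysis, if chosen instead, costs a further training run. Reported accuracy may be less favourable.

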**Fig 2 pone.0268535.g002:**
[figure not shown]
General flow of processing collected data.

Collected teeth models will be randomly divided into **training** and **validation** sets.

At least two-hundred **training** sets including the **original** and the **processed** models will be input into the AI system to learn the relationship between individual teeth (tooth 16) and rest of the dentition via a 3D Generative Adversarial Network (GAN) designed for this study (Fig 3). Data will be computed by the High-Performance Computer provided by the Information Technology Services (ITS), The University of Hong Kong (HKU), which is capable of conducting data intensive and accelerated computing using a high-performance computing cluster with an aggregating processing power of 804 TFlop/s (Fig 4).

**Fig 3 pone.0268535.g003:**
[figure not shown]
Brief architecture of the Generative Adversarial Network (GAN) of this study. Original model: digitized maxillary teeth model collected from participants; processed model: teeth model with tooth 16 removed; Generated model: teeth model with AI-generated tooth 16.

